#### Design

The RCT will be a multi-site, non-blinded, parallel-group study with two independent population arms to determine the efficacy and safety of the new model of care (LivR Well) compared to standard care and to inform a cost-effectiveness analysis.

This study protocol was developed in line with Recommendations for Interventional Trials (SPIRIT) guidelines including the SPIRIT checklist [17], which has been adapted in accordance with World Health Organisation registration (Appendix 1) and the CONSORT extension to pilot and feasibility trials [18] (Table 3, Appendix 2).

**Table 3 Tab3:**
[figure not shown]
Standard Protocol Items: Recommendations for Interventional Trials (SPIRIT) figure

t_1_ 28 days after allocation, t_2_^a^ week 6 follow-up, t_3_^b^ week 12 follow-up

^c^Changes in liver disease severity, quality of life, and cost-effectiveness compared to standard care

^d^(a) Source of referral, (b) re-enrolment after unplanned hospitalisation, (c) COVID-19, and (d) hepatic decompensation without ACLF

#### Participants and setting

The study context is a multicentre tertiary health service in Melbourne, Australia with recruitment from three tertiary hospital campuses. Monash Health is the second largest healthcare service in Australia managing a catchment population greater than 1.2 million people [19], which includes the largest Culturally and Linguistically Diverse (CALD) community, the significant burden of socioeconomic disadvantage and the highest unemployment rates in the state of Victoria [20]. The 28-day intervention will be delivered through ‘Hospital in the Home’ (HITH), a medically-led ambulatory care programme supported by physical clinics and home visits by the nursing team. HITH is able to deliver many aspects of acute hospital care in the community to otherwise stable patients including diagnosis and management of acute conditions that would typically require bed-based care

Patients will have access to up to three home visits per week by nursing staff and physiotherapists. The patients will attend a hospital-based ambulatory care liver clinic weekly for a medical and nursing review with a dietitian, social work, addiction medicine, and pharmacist consultations as required. Patients will be referred to LivR Well from an outpatient context, the emergency department or the inpatient ward. Patients with any severity of liver disease are eligible unless receiving end-of-life care. There are no cut-offs for the MELD score or Child Turcotte Pugh score.

#### Inclusion criteria

##### Adult patients

with previous or current hepatic decompensation defined as presence of ascites, hepatic encephalopathy, and/or variceal haemorrhage [21].with or without a diagnosis of acute-on-chronic liver failure (ACLF) using the European Foundation for the Study of Chronic Liver Failure criteria (EF-CLIF) including age and white cell count. Severity is graded according to the number of organ failures (Tables 1 and 2) [14].Requiring consultation from ≥3 allied health clinicians (Table 4)

**Table 4 Tab4:** Allied health referrals

Clinician	Indication for referral	Tasks
Physiotherapist	Sarcopenia^a^, fall within last 6 months, FRAT^b^ score >11	6-min walk test (baseline and at day 28) Weekly, supervised low-intensity weight and resistance exercises
Dietitian	Sarcopenia, diabetes, alcohol dependence, MUST^c^ score ≥2	High protein, high energy, low salt diet plan incorporating compact nutritional supplements including a late-night snack
Social Work	Requiring long-term home support services, established disability, age >65 years	Referral for council services, aged care assessment, disability
Neuropsychiatry	Concern from the medical team regarding cognition	Neuropsychiatric assessment
Pharmacist	Polypharmacy (≥5 medications daily) and/or requiring titration of diuretic or lactulose doses	Patient and carer education, liaising with community pharmacy, organise blister pack
Addiction Medicine	Substance use disorder and alcohol pharmacotherapy	Weekly consultations, pharmacotherapy to manage substance use disorders

^a^Sarcopenia is defined using the European Working Group on Sarcopenia in Older People (EWGSOP) hand grip strength cut off (<27kg for males, <16kg for females) [22]

^b^
*FRAT* Falls Risk Assessment Tool [23]

^c^
*MUST* Malnutrition Universal Screening Tool [24]

##### Defining ACLF

The diagnosis and grading of ACLF will be performed using the publically-available online calculator incorporating this formula: 10×[0.33×CLIF-OFs + 0.04×Age + 0.63×Ln (White cell count) − 2] [13]. (Tables 1 and 2)SI units of measurement (μmol/L) will be converted to mg/dL for serum bilirubin and serum creatinine for use in the calculator.

#### Exclusion criteria

Greater than grade 2 hepatic encephalopathySevere chronic extrahepatic diseaseActive malignancy including hepatocellular carcinomaInability to provide informed consentResiding outside the local hospital service catchment or deemed ineligible for home visits due to staff safety or occupational hazard concernsResiding in a residential aged care facility

N.B. Concurrent COVID-19 infection is not an exclusion criterion.

##### Prohibited concomitant care

Admission for scheduled procedure or treatmentMoribund or receiving end-of-life careReceiving regular albumin infusions for the treatment of diuretic refractory ascites or chronic hepatorenal syndrome (excluding those for periprocedural circulatory support following large volume paracentesis)Refractory ascites managed with an intra-peritoneal catheter in-situ

#### Processes, interventions and comparisons

LivR Well is a 28-day intensive liver optimisation programme delivered at home and through the outpatient clinic. It is an innovative multidisciplinary model of care co-developed with patients and carers including delivery system re-design (home-based nursing, weekly medical reviews, regular dietitian and pharmacy consults) and adjunct interventions including enteral nutrition for sarcopenia, physiotherapy, large volume paracentesis, addiction medicine consultation and neuropsychiatric assessment for cognitive impairment/hepatic encephalopathy. Referrals to allied health clinicians will be made based on indications outlined in Table 4.

Patients will be enrolled on discharge from the acute admission, directly from the emergency department or the outpatient clinic as demonstrated in the Patient Journey Map (Fig. 1). A standardised checklist template (Appendix 3) will be completed on admission. Patients will have an in-home clinical review by a nurse up to three times per week with observations and blood tests taken weekly, or as requested by the clinic gastroenterologist. A face-to-face appointment at the ambulatory complex care liver clinic will occur weekly and will provide medical and nursing reviews with the opportunity for a dietitian, pharmacist and social worker consultations as required. Key time points and tasks for completion are outlined in Table 5.

**Fig. 1 Fig1:**
[figure not shown]
Patient journey map

**Table 5 Tab5:** Key time points and tasks for completion

	Day 1	28-day programme	Week 6	Week 12
Timeframe for completion	Within 3 days	Weekly	Within 7 days	Within 2 weeks
Tasks	Blood tests EQ-5D CLDQ	Blood tests Complex Care Liver Clinic	Blood tests DQ-5D CLDQ	Blood tests Complex Care Liver Clinic

Patients on the LivR Well programme will be remotely monitored in between clinic appointments through a custom-built app paired to a Bluetooth scale. Patient-reported outcome measures (PROMS) including quality of life, will be collected through a mobile phone text message link to the online surveys. Patients will also be able to access Lucy LiverBot, a custom-built artificial intelligence ChatBot for all disease-related questions. Quality of life assessments will be performed at day 1 and longitudinally at 6 weeks and 12 weeks from admission in both arms of the RCT. Two validated instruments will be used [EuroQol 5 Dimensions (EQ-5D) [25] and Chronic Liver Disease Questionnaire (CLDQ)] [26]. Outcomes from these assessments will guide the economic evaluation for a cost-effectiveness analysis. Adherence will be monitored through recording attendance at appointments, home visits and regular urinary ethyl glucuronide tests, a biomarker of alcohol consumption [27].

The comparator will be outpatient management in a ‘complex care liver clinic’, an ambulatory care clinic for patients with decompensated cirrhosis, promoting continuity of care by a gastroenterologist, hepatology nurse and pharmacist through regular face-to-face appointments. The control cohort will have no access to the additional allied health clinicians, technology aids or home visits through the LivR Well programme.

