#### Recruitment

Patients will be recruited from the following settings: (a) following an acute hospital admission, (b) directly from the emergency department if able to be discharged home or (c) from the complex liver care clinic if ACLF or decompensation develops. All patients will be assessed by a gastroenterologist and allied health clinicians prior to recruitment. A research assistant or Pharmacist Informatician will provide eligible patients with a Participant Information and Consent Form (PICF) (Appendix 4) and consent will be obtained by a sub-investigator. Patients will be reviewed and admitted to the programme on the day of enrolment. All patients receiving LivR Well will also be onboarded to a mobile application and provided with the requisite hardware and software. Participants will be discontinued from the trial if consent is withdrawn, or if a serious adverse event (as defined on page 9) or death occurs. All participants will be included in the intention-to-treat analysis. If patients are admitted to the hospital after enrolment but before completion, the 28-day programme can be re-started on discharge if the patient still meets eligibility criteria and at the discretion of the treating team.

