#### Screening and randomisation

Patients will be screened against inclusion and exclusion criteria at the time of diagnosis of ACLF or hepatic decompensation. Those who meet the criteria will be enrolled into the study and provided informed consent. These recruited patients will be randomised in a 1:1 ratio to either the LivR Well programme or to complex care liver clinic in the control arm. Participants will be computer randomised and informed of their allocation by the CLD nurse specialist prior to discharge or within 24 hours of obtaining informed consent. Patients from both study arms will be registered on the Virtual Hospital masterlog through the Microsoft Power Apps program. Due to the nature of the intervention, blinding of study participants or clinical staff administering the LivR Well programme will not be possible. However, outcome ascertainment for the primary outcome, as well as the health services utilisation secondary outcomes will be blinded. Furthermore, all data analyses will be undertaken in a blinded manner. The statistician will be blinded to the feasibility study data results and the treatment allocation of the RCT.

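### The three-day window for the Day 1 EQ-5D and CLDQ lets some baselines be recorded after patients know their open allocation, which could bias week-6 quality-of-life change

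*Protocol article*

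**What the plan says.** Under Outcomes, quality of life (CLDQ and EQ-5D) is a secondary outcome, assessed at week 6 against baseline. Under Processes, interventions and comparisons, the text says that "Quality of life assessments will be performed at day 1 and longitudinally at 6 weeks and 12 weeks from admission in both arms". Table 5 lists the Day 1 tasks as "Blood tests EQ-5D CLDQ" and allows three days to complete them. Patient-reported measures "will be collected through a mobile phone text message link to the online surveys".

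Under Screening and randomisation, participants are randomised by computer and "informed of their allocation by the CLD nurse specialist prior to discharge or within 24 hours of obtaining informed consent". The same section says that "blinding of study participants or clinical staff administering the LivR Well programme will not be possible". It limits blinded assessment as follows: "outcome ascertainment for the primary outcome, as well as the health services utilisation secondary outcomes will be blinded". Quality of life is not on that list. Under Recruitment, "Patients will be reviewed and admitted to the programme on the day of enrolment".

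Statistical analyses names t-tests or non-parametric equivalents for continuous outcomes. It does not say whether week-6 quality of life is analysed as a raw score, as a change, or with baseline adjustment. The questionnaire results also guide the economic evaluation.

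**The concern.** A baseline is protected by randomisation only if it is measured before the patient can react to the allocation. Here the stated rules allow the opposite order. By the time the questionnaire is answered, an intervention patient may have been told the arm, reviewed and admitted to the programme. A control patient may know that home visits, technology aids and the additional allied health clinicians are not on offer. Self-reported items on worry or mood could respond to that news. The feasibility study reported week-6 improvement in the CLDQ worry and fatigue domains, so a responsive domain is among those of interest.

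If baselines differ by arm for this reason, the difference passes into the week-6 change with opposite sign and could create or hide an effect. Adjusting for the same baseline reduces the problem but does not remove it, because the covariate is itself a post-randomisation measure. Utilities adjusted for baseline EQ-5D would carry the same fault. No later analysis can fully recover a clean baseline.

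**Working it through.** **Order of events.** The protocol gives no figure to reproduce here, so the first step is to set the stated times side by side.

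| Event | Stated time | Section |
|---|---|---|
| Admission to the programme | Day of enrolment | Recruitment |
| Patient told the arm | Before discharge, or within 24 hours of consent | Screening and randomisation |
| EQ-5D and CLDQ baseline | Day 1, with three days to complete | Table 5 |

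Table 5 does not define Day 1. If it is the day of consent and enrolment, and the 24-hour limit applies, about 3 − 1 = 2 days of the window fall after disclosure. An inpatient told the arm on the ward can also answer the text link after discharge and still comply. The text sets no rule that the questionnaires come first.

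**Illustration of size.** The documents give no shift, SD or correlation, so these are assumptions:
- baseline and week-6 SD both 1, correlation ρ = 0.5, no true effect;
- an average between-arm baseline shift s of 0.1, 0.2 or 0.3 SD, absent from the week-6 score;
- evaluable patients per arm from Sample size: 160 × 0.8 = 128 (hepatic decompensation) and 60 × 0.8 = 48 (ACLF);
- two-sided 5% test, normal approximation.

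Rejection rate = 1 − Φ(1.96 − e) + Φ(−1.96 − e), where e is bias divided by standard error.

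*Unadjusted change score.* The bias has size s. The SD of change is √(2(1 − 0.5)) = 1, so SE = √(2/n): 0.125 for n = 128 and 0.204 for n = 48. With n = 128, e = 0.80, 1.60 and 2.40.

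*Baseline-adjusted analysis.* The bias has size ρs = 0.5s. SE = √((1 − 0.5²) × 2/n): 0.108 for n = 128 and 0.177 for n = 48. With n = 128, e = 0.46, 0.92 and 1.39.

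| Shift s | 128 per arm, change score | 128 per arm, adjusted | 48 per arm, change score | 48 per arm, adjusted |
|---|---|---|---|---|
| 0 | 5.0% | 5.0% | 5.0% | 5.0% |
| 0.1 SD | 12.6% | 7.5% | 7.8% | 5.9% |
| 0.2 SD | 36.0% | 15.2% | 16.5% | 8.7% |
| 0.3 SD | 67.0% | 28.3% | 31.2% | 13.6% |

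The result depends on the correlation. With ρ = 0.7 and 128 per arm, the rates over the three shifts are 17.8%, 54.2% and 87.3% for the change score, and 12.3%, 34.8% and 65.3% with adjustment.

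**Partial late completion.** The shift s is an average over the whole arm. If a fraction f answers late and the reaction among them is r, then s = f × r. For example, a 0.3 SD reaction in one third of patients gives s = 0.1 SD, which is the second row of the table.

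**After the fix.** With questionnaires completed before allocation is known, the expected shift is 0 and the first row applies.

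**The case against.** The strongest reply is that the order may be settled elsewhere. The SPIRIT schedule (Table 3), the Patient Journey Map (Fig. 1) and the admission checklist (Appendix 3) are not in the text at hand, and Table 3 may place baseline before allocation. The Table 5 timeframe gives no direction, and same-day completion before disclosure fits the wording. This stands as a limit on certainty. It does not remove the point, because a three-day allowance for Day 1 tasks naturally permits later completion and would still have to be reconciled with Table 3.

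A second reply is that the analysis model is not fixed. That also stands. A plain week-6 comparison would not carry the bias at all, and at correlation 0.5 baseline adjustment halves it.

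A third reply is that week-6 answers are open-label self-report whenever the baseline is taken. This is true, and the fix does not cure it. It is no reason to leave an avoidable bias in the baseline as well.

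Three stronger readings are tempting but not supported:
- **That many or most baselines will be late.** No figure in the protocol supports this. The rules permit late completion, and how often it would happen is unknown.
- **That the time origin for later visits does not exist for controls.** The word admission could mean hospital admission, which some patients in either arm have had. It is ambiguous, and that is a separate matter from the baseline.
- **That baseline blood tests must also precede randomisation.** They share the window, but nothing here shows that laboratory values react to news of allocation.

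**Conclusion.** The point holds in a limited form. As written, the protocol allows some baseline EQ-5D and CLDQ scores to be collected after open allocation is known and, in the intervention arm, after the programme has begun. This could bias week-6 change from baseline and any baseline-adjusted utilities. Neither primary outcome is affected.

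The size and direction cannot be determined from the protocol. The rates in the table follow from assumed whole-arm shifts and an assumed correlation. A reader might take the 67% figure as the error rate of this trial, but it describes the most extreme assumed shift at correlation 0.5, analysed as an unadjusted change score. The conclusion rests on reading Day 1 as the enrolment day and on Table 3 not already setting a stricter order. It merits correction because the change is cheap and the damage cannot be fully repaired at analysis.

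**What to change.** In Table 5 and in Screening and randomisation, state that EQ-5D and CLDQ are completed after consent and before the allocation is generated or disclosed, for example by text link or on a device at the consent visit. Remove the three-day allowance for these two questionnaires, and make Table 3 agree. Baseline bloods need not hold up randomisation.

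The cost is protocol wording and a check in the order of steps, with no added assessment. The downside is a short delay in randomisation or disclosure, felt mainly by patients enrolled directly from the emergency department.

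Separately, reconcile the admission-based origin for the week 6 and week 12 questionnaires with the Abstract, which counts follow-up from randomisation, and with the Table 3 footnote, which counts the 28-day time point from allocation.

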#### Recruitment

Patients will be recruited from the following settings: (a) following an acute hospital admission, (b) directly from the emergency department if able to be discharged home or (c) from the complex liver care clinic if ACLF or decompensation develops. All patients will be assessed by a gastroenterologist and allied health clinicians prior to recruitment. A research assistant or Pharmacist Informatician will provide eligible patients with a Participant Information and Consent Form (PICF) (Appendix 4) and consent will be obtained by a sub-investigator. Patients will be reviewed and admitted to the programme on the day of enrolment. All patients receiving LivR Well will also be onboarded to a mobile application and provided with the requisite hardware and software. Participants will be discontinued from the trial if consent is withdrawn, or if a serious adverse event (as defined on page 9) or death occurs. All participants will be included in the intention-to-treat analysis. If patients are admitted to the hospital after enrolment but before completion, the 28-day programme can be re-started on discharge if the patient still meets eligibility criteria and at the discretion of the treating team.

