**Methods:**

We will recruit adult patients with chronic liver disease from the emergency departments, in-patient admissions, and an ambulatory liver clinic of a multi-site quaternary health service in Melbourne, Australia. A total of 120 patients meeting EF-Clif criteria will be recruited to the ACLF arm, and 320 patients to the hepatic decompensation arm. Participants in each cohort will be randomised to the intervention arm, a 28-day multidisciplinary programme or to standard ambulatory care in a 1:1 ratio. The intervention arm includes access to nursing, pharmacy, physiotherapy, dietetics, social work, and neuropsychiatry clinicians. For the ACLF cohort, the primary outcome is 28-day mortality. For the hepatic decompensation cohort, the primary outcome is 30-day re-admission. Secondary outcomes assess changes in liver disease severity and quality of life. An interim analysis will be performed at 50% recruitment to consider early cessation of the trial if the intervention is superior to the control, as suggested in our feasibility study. A cost-effectiveness analysis will be performed. Patients will be followed up for 12 weeks from randomisation. Three exploratory subgroup analyses will be conducted by (a) source of referral, (b) unplanned hospitalisation, and (c) concurrent COVID-19. The trial has been registered with the Australian New Zealand Clinical Trials Registry.

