#### Adverse events

Adverse events are defined as “any untoward medical occurrence in a patient or clinical trial participant”. Serious adverse events (SAEs) will be defined as …” an untoward occurrence that results in death; is life-threatening; requires hospitalisation or prolongation of existing hospitalisation; results in persistent or significant disability or incapacity; consists of a congenital anomaly or birth defect” [28]; and will be reported to the PI and local ethics committee immediately. Any patients suffering harm from the trial will receive post-trial care in the liver clinic. Adverse event and SAS data will be collected in the same Power BI database at the time of occurrence by the hepatology nurse consultant.

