#### Interim analysis

A data monitoring committee will consist of 3 senior independent clinician researchers without competing interests. An interim analysis will be conducted and we will adopt a Bayesian approach for an adaptive trial design where efficacy and futility criteria will be based on the probability of treatment effects, given the observed data in our feasibility study. One interim analysis will be performed in the ACLF and decompensated cohort when 50% of patients have been randomised and have completed 12 weeks of follow-up. We will stop the RCT for efficacy if the posterior probability (Pr) that the hazard ratio (HR) is < 1 is > 90% (Pr (HR <1|data) > 0.9. Similarly, we would stop for futility if Pr (HR <1|data) < 0.1. The results are reviewed by the independent data monitoring committee who will ultimately guide the decision to continue or cease the study.

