#### Statistical analyses

The data analysis for the primary composite endpoint of death, referral for liver transplantation or 30-day readmission from the date of hospital discharge will be undertaken on an intention-to-treat basis. A 28-day mortality rate will be calculated from the date of randomisation. For the primary and other binary outcomes, chi-squared tests will be used to compare the intervention and control groups. Survival analyses will also be undertaken, with the generation of Kaplan-Meier curves and Cox regression analyses to derive (adjusted) hazard ratios. For continuous outcomes, t-tests or non-parametric equivalents (e.g., Mann-Whitney tests) will be applied to compare the intervention and comparator groups. A *p* value of 0.05 is considered significant and 95% confidence intervals will be reported for all effect estimates Three exploratory subgroup analyses are planned: (a) comparing groups by the source of referral—conducted to address bias created following randomisation whereby in-patients in the intervention arm may be discharged home earlier due to perceived safety with regular home visits compared to those in the control arm. This subgroup analysis will account for differences between those admitted from in-patient admission compared to the emergency department or the ambulatory liver clinic; (b) comparing groups by re-enrolment to LivR Well after drop out due to unplanned re-admission to hospital. Data from the first enrolment to LivR Well will be included in the primary outcomes on an intention-to-treat basis and (c) patients with COVID-19 at the time of referral. Analyses will be performed using Stata statistical software, version 16.1 for Mac (StataCorp, College Station, TX, USA).

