#### Economic analysis

The economic analysis will examine the cost-effectiveness of the LivR Well programme compared to the less resource-intensive control arm and will include both health system and societal cost perspectives. The main output of interest is the incremental cost-effectiveness ratio (ICER) in terms of net costs per unit of health gain. Health gains will be measured in clinical outcomes, estimation of years of life gained, quality-adjusted life years (QALYs) gained and by collection of quality-of-life data. Net costs will comprise the differential costs of the LivR Well programme and usual care minus costs saved from reduction in downstream health service utilisation. All health economic analyses will be undertaken in accordance with recommended approaches such as 5% discounting of estimated future costs and health gains. To account for any uncertainty in the data inputs for health economic modelling, sensitivity and uncertainty analyses will be undertaken via Monte Carlo simulation [31].

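### As written, a serious adverse event, which includes an unplanned readmission, ends trial participation; this contradicts the restart and re-enrolment rules and puts later secondary outcomes at risk

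*Protocol article*

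**What the plan says.** All references are to the protocol article.

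- **Discontinuation (Recruitment).** "Participants will be discontinued from the trial if consent is withdrawn, or if a serious adverse event (as defined on page 9". The sentence closes by adding death. It speaks of participants and of the trial, so it covers both arms and is not confined to the LivR Well programme.
- **Definition (Adverse events).** A serious event includes an untoward occurrence that "requires hospitalisation or prolongation of existing hospitalisation".
- **Restart (Recruitment, same paragraph).** For patients admitted after enrolment, "the 28-day programme can be re-started on discharge", subject to continued eligibility and the treating team's judgement.
- **Re-enrolment (Statistical analyses).** One exploratory subgroup is defined as "comparing groups by re-enrolment to LivR Well after drop out due to unplanned re-admission to hospital". Data from the first enrolment count in the primary outcomes.
- **Follow-up.** The Abstract says "Patients will be followed up for 12 weeks from randomisation". The Interim analysis takes place "when 50% of patients have been randomised and have completed 12 weeks of follow-up".
- **Later outcomes.** The Outcomes section sets MELD and Child-Pugh at day 28 and week 12, and quality of life at week 6. Processes, interventions and comparisons schedules EQ-5D and CLDQ "longitudinally at 6 weeks and 12 weeks from admission in both arms of the RCT".

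**The concern.** In this population an unplanned readmission is common, and it is the primary outcome of the decompensation cohort. A rule that removes a participant from the trial on a hospitalising event is therefore triggered by an outcome. Staff who follow the sentence would stop the scheduled bloods and questionnaires for patients who had just deteriorated.

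The loss would differ between arms whenever readmission differs. If controls are readmitted more often, as the design expects, and if readmitted patients later do worse, the sicker controls leave the later comparisons and a benefit of LivR Well is understated. The Discussion also allows close follow-up to bring LivR Well patients back to hospital faster; in that case a harm could be understated.

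The restart provision does not repair this. It restarts a programme that controls never receive, and only at clinicians' discretion. If staff resolved the conflict by keeping restarted patients under observation, readmitted LivR Well patients would have a route back into follow-up and readmitted controls would have none, in an unblinded trial.

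**Working it through.** **1. Do the statements agree?**

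| Statement | Consequence for a patient with an unplanned readmission |
|---|---|
| Recruitment (discontinuation) with Adverse events (definition) | Out of the trial, either arm |
| Recruitment (restart) | May restart the 28-day programme |
| Statistical analyses (subgroup) | May re-enrol and is analysed as a subgroup |
| Abstract, Interim analysis | Followed to 12 weeks |
| Outcomes; Processes, interventions and comparisons | Assessed at day 28, week 6 and week 12 |

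The restart and re-enrolment rows contradict the first row. The follow-up and assessment rows are general schedules, to which a discontinuation rule could make exceptions. They do not fit the first row, but they conflict with it less sharply. A planned admission is not an untoward event and is not caught.

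**2. Reproducing the decompensation sample size.** Inputs from Sample size: two-sided 5%, 80% power, 20% dropout, 17% readmission with LivR Well, 160 per arm. No single control rate is stated, only a published range of 17% to 38%, so I solved for it.

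n per arm = [1.96 √(2 p̄(1 − p̄)) + 0.8416 √(pC(1 − pC) + pT(1 − pT))]² / (pC − pT)²

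With pC = 0.32, pT = 0.17 and p̄ = 0.245:

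- first term 1.96 × √0.36995 = 1.192
- second term 0.8416 × √0.3587 = 0.504
- n = (1.696)² / 0.0225 ≈ 128; 128 / 0.8 = 160 per arm, 320 in total, as stated

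With a continuity correction, 33% gives 126, then 158 per arm (316 in total). A control rate of about 32% to 33% is therefore consistent with the plan, but it is inferred.

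**3. How many would leave by day 30 under the literal rule?** Assumptions: every readmission in the quoted rates is untoward, and the rates apply to emergency-department and clinic recruits as well. Number leaving = 160 × rate in each arm.

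| Control rate | LivR Well (17%) | Control | Total of 320 | Share |
|---|---|---|---|---|
| 17% | 27.2 | 27.2 | 54.4 | 17.0% |
| 32% (back-solved) | 27.2 | 51.2 | 78.4 | 24.5% |
| 38% | 27.2 | 60.8 | 88.0 | 27.5% |

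At 32%, about 133 LivR Well patients (160 − 27.2) and 109 controls (160 − 51.2) would remain for week 6 and week 12. Patients readmitted before day 28 would also lose the day-28 MELD and Child-Pugh.

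**4. Primary outcomes.** In the decompensation cohort the first readmission within 30 days is the event and is recorded as it triggers discontinuation, so nothing is lost. In the ACLF cohort a patient readmitted before day 28 who then dies before day 28 could be missed. The documents give no share of deaths that follow this path, so I give no count.

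**The case against.** The strongest reply is that the authors meant discontinuation from the programme. The same paragraph places everyone in the intention-to-treat analysis and allows a restart, and Statistical analyses speaks of re-enrolment to LivR Well. Screening and randomisation describes blinded ascertainment of the primary outcome and of health service utilisation, and Data collection lists admissions and deaths. The article also condenses a fuller protocol.

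Much of this stands. The programme reading is probably the intended one, and deaths, admissions and utilisation would probably still be captured. But the sentence says trial, and it sets serious adverse events beside death and withdrawal of consent, which ordinarily end follow-up. Intention-to-treat says who is analysed; it does not supply measurements that were never taken. No section says that bloods or questionnaires continue after discontinuation. This is a rule stated wrongly, not a detail left to another document.

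Four stronger readings are tempting and are not supported:

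- **The loss exceeds the 20% dropout allowance.** That allowance belongs to the primary-endpoint calculation. A readmitted decompensation patient has already supplied that endpoint and is not a dropout for it.
- **The bias has a known size.** Any figure would need an assumed outcome gap between readmitted and other patients, and an assumption about the programme's direct effect. The documents give neither.
- **Repeat admissions and their costs are lost.** The Economic analysis does depend on "usual care minus costs saved from reduction in downstream health service utilisation", but the ascertainment statements point to continued capture of utilisation. The only admission price given is for ACLF, so it would not price a decompensation readmission.
- **The counts are a minimum.** Later readmissions would add to them, but scheduled admissions within the quoted rates, or lower rates in emergency-department and clinic recruits, would reduce them.

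**Conclusion.** The point holds in a limited form. As written, the discontinuation sentence and the definition of a serious adverse event together remove a participant from the trial at an unplanned readmission, against the restart and re-enrolment rules and out of line with 12-week follow-up. The exposure is mainly MELD and Child-Pugh at day 28 and week 12, and EQ-5D and CLDQ at weeks 6 and 12, in readmitted patients of either arm.

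In the decompensation cohort that is about 27 of 160 LivR Well patients and 27 to 61 of 160 controls. These figures depend on literal application of the rule, on the quoted readmissions being untoward and, for the central value of about 78 in total, on the inferred control rate.

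A reader might infer that the primary comparisons are compromised. The decompensation primary outcome is not. For ACLF mortality there is only a possibility, and the described ascertainment of deaths makes it less likely. The point is worth correcting because site staff act on this sentence before any analysis begins, and a missed questionnaire or blood test cannot be recovered.

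**What to change.** Reword the sentence in Recruitment so that a serious adverse event or unplanned readmission may pause or stop the LivR Well programme but does not end trial follow-up. State that only death or withdrawal of consent to data collection ends follow-up. Add that vital status, all admissions, MELD and Child-Pugh, and EQ-5D and CLDQ are collected at their scheduled times to week 12 for every randomised participant in both arms, whether or not the programme continues or restarts.

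The cost is a short protocol correction, plus continued data collection from readmitted participants at visits already scheduled and from hospital records. The downside is small.
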